#### Recruitment

The participating study sites collectively attend 8.326 cases per year (reference year, 2022) with an average of 757 annual and 63 monthly cases. According to the sample size calculation, 11 patients per study site per month should be enrolled, representing approximately 35% of the eligible case volume after subtracting 50% of the total case number due to assumed ineligibility. To account for regional and seasonal variations of TBI incidence and recruitment success, a maximum number of 13 recruited patients per center per month will be allowed.

The study’s core team has ensured close engagement of the study sites throughout the grant application process and will continue to do so by providing continuous on-site and virtual support, information material, and financial compensation for recruitment. If recruitment difficulties arise in one study site, higher case numbers could be permitted for one or more well-recruiting study sites, or additional study sites could be onboarded.

Caregivers of potentially eligible patients will receive study information immediately during the initial triage by the ED staff, thereby making use of the waiting time for preliminary information.

### Assignment of interventions and blinding

The randomization of the clusters will be carried out by one of the independent study’s evaluators (Institute for Medical Informatics, Biometry, and Epidemiology of the University Hospital Essen; IMIBE) using appropriate software. The core team will receive information on the start date with appropriate lead time and pass this information on to the study sites that will enroll patients.

The core team and attending local ED staff cannot be blinded for the assignment group, because implementing and performing the nCP involves their active participation. All evaluators will be blinded for the assignment group until the end of analyses. Unblinding will be performed by a trusted third party (TTP).

### Data collection, management, and analysis

#### Data collection and management

Clinical data including the two co-primary outcomes (CPO) are documented via the eCRF that includes a trial participant management system for the attending physicians (hospitalization, re-visit at the same hospital) or via a final query in the parent app/telephone follow-up (re-presentation at different hospital): If a patient returns to the same hospital within 72 h after discharge home, the patient case is reactivated in the eCRF and relevant treatment data is recorded, including time of presentation; reason for presentation; presentation related to head injury; consequences (imaging, outpatient management, hospitalization, type of hospitalization, need for neuro/cranial surgery); and outcome (neurological status at discharge, death). For phone calls from caregivers within 72 h after initial presentation, the case is reopened in the eCRF and documentation is supplemented with information about call time, reason, relation to head injury, and consequences by the attending physician.

During home monitoring in the intervention group, parents will enter data times at the time points specified to assess their child’s condition (2, 6, 12, 24, and 48 h after ED presentation) for the study documentation.

In routine clinical care, patients may present to hospitals other than their initial treating facility. For this purpose, an automated query is sent via the parent app 72 h after presentation to the ED. This final query requests information about whether caregivers have visited an ED, hospital, emergency services, or pediatrician within 72 h after discharge from the ED. If confirmed, follow-up questions address whether the visit was related to the head injury and its consequences. If the query is not answered within 5 to 7 days after discharge in the smartphone app, parents will receive a phone call to verify the endpoint “unplanned re-visit” by the local study team. The control group receives their phone call 72 h to 7 days after presentation to the ED with the documentation as for the intervention group.

For cases with fatal outcomes after the 72-h active query period, passive surveillance remains possible through reporting by participating sites until the completion of data collection for the entire study.

After meeting the monthly recruitment target, the local study physicians will document eligible but non-approached cases using the same software as for the study documentation anonymously.

Additionally, anonymized retrospective data collection will be performed as a historical control cohort at each study site, covering a 12-month period before initiation of the SaVeBRAIN.Kids project (September 2023–August 2024). This control cohort serves as a comparison group to assess possible effects attributable to project training and use of the structured eCRF. The inclusion criteria for this cohort are the same as for the control- and intervention group. This data is transmitted to the TTP by each study site to verify that no personal data is included, concatenated, and forwarded to the clinical evaluator (IMIBE) for statistical analyses.

The basis for the healthcare economic evaluation is billing data from the enrolled patients who are insured with one of the consortium’s statutory health insurances. This includes the pseudonymized merging of the routine data with clinical data, which were documented during the survey period in the eCRF and parent app, at the TTP. The routine data for outpatient physcian visits, medical aids, medication, rehabilitation measures funded by statutory health insurance, and hospital stays are included. The expenses for the nCP compared to standard care will be estimated through personnel deployment, using time stamps in the eCRF. Additionally, investment, material, and personnel costs for the implementation of the intervention, as well as the costs for staff training, will be assessed. The overall cost analysis from billing data is conducted for the period 1 week before and after the trauma, with sensitivity analysis 1 month before and after the trauma.

During treatment and observation in the ED, the following time stamps are automatically recorded in the eCRF, which will be used for the health economic evaluation: beginning and end of (a) medical history taking, (b) of the body check, (c) of the neurological examination, (d) until the further procedure is initiated, and (e) of symptom-oriented monitoring (Fig. 2). Additionally, in each ED time spent on collecting GCS, pupil reflexes, and vital signs as part of the monitoring process will be assessed for 10 patients to derive the costs associated with the monitoring process. As part of the process evaluation, parents will be surveyed regarding their acceptance of the medical measures and potential improvements via an eCRF in LimeSurvey (LimeSurvey GmbH, Hamburg, Germany) using their child’s study pseudonym. Letters requesting participation will be handed out by the study sites, containing a QR code for accessing the online survey and for the parent app users a directed link after the 72-h questioning will appear. ED staff will be queried via anonymous LimeSurveys. The data flow throughout the project is detailed in Fig. 3.

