**Methods:**

The SaVeBRAIN.Kids trial will implement and test a novel care pathway (nCP) for evidence-based standardized risk assessment, structured observation in the emergency department (ED) for several hours, and technology-supported home monitoring with the aim to reduce hospitalizations. This non-inferiority multicenter study will be carried out using a cluster-randomized stepped-wedge design, with all centers starting in the control phase and sequentially transitioning to the intervention. Eligible participants (age ≥ 3 months and < 18 years) must present within 48 h of head injury, have minimal symptoms (Glasgow coma scale ≥ 14), and no risk factors for intracranial complications. The co-primary outcomes are the relative risk of hospitalization and the proportion of unplanned re-visits within 72 h of presentation to the ED for ambulatory cases. Secondary outcomes include clinical safety measures, cost-effectiveness, and process evaluation. Based on power calculations (*α* = 0.05, power = 0.9), 1390 patients will be recruited over 12 months.

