The SaVeBRAIN.Kids trial will evaluate a novel care pathway (nCP) for children with mTBI that was designed to (1) standardize management of mild TBI; (2) implement the option of a short-term symptom-oriented observation in the emergency department (ED) instead of immediate hospital admission; (3) support caregivers during home monitoring via a specifically designed smart phone app. The aim of the nCP is to reduce the proportion of hospitalizations among pediatric patients with mTBI, who are at very low risk for relevant intracranial complications while maintaining equivalent medical safety to the current standard of care. The study will be carried out as a non-inferiority trial using a multi-centered cluster-randomized stepped-wedge design with the hospitalization rate and unplanned re-visits within 72 h from ED discharge as co-primary outcomes.

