##### Primary outcomes

 1st Co-primary outcome: Relative risk of hospitalization among all included cases (outpatient and inpatient) at initial ED presentation.

2nd Co-primary outcome: Proportion of cases with unplanned re-visit within 72 h after discharge from the ED.

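### The 72-hour re-visit co-primary has no single time zero or denominator, and its app query goes out before the window it asks about has closed

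*Protocol article*

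**What the plan says.** All references are to the protocol article.

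**Time zero and denominator**
- Abstract (Methods): "the proportion of unplanned re-visits within 72 h of presentation to the ED for ambulatory cases".
- Introduction: "unplanned re-visits within 72 h from ED discharge as co-primary outcomes".
- Primary outcomes: the proportion of cases with a re-visit in the 72 hours "after discharge from the ED", with no restriction to ambulatory cases.
- Data collection and management, same-hospital returns: the rule counts 72 hours "after discharge home, the patient case is reactivated in the eCRF". Caregiver telephone calls in the same paragraph are timed from initial presentation.

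**Follow-up contact (Data collection and management)**
- Intervention phase: "an automated query is sent via the parent app" 72 hours after presentation. The question it puts to parents covers the 72 hours after ED discharge. A telephone call follows only "If the query is not answered within 5 to 7 days after discharge in the smartphone app".
- Control phase: one telephone call, between 72 hours and 7 "days after presentation to the ED with the documentation as for the intervention group".

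**The concern.** A co-primary outcome needs one time zero and one denominator. Here the reader can assemble more than one endpoint from the same article. The wording also carries into data capture, because the eCRF re-activation rule, the app trigger and the query text each fix what is recorded. An analysis plan cannot recover a re-visit that was never asked about.

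The trigger also conflicts with its own question. ED discharge comes after presentation, so a query sent 72 hours after presentation is always sent while part of its 72-hour window is still open. The nCP adds ED observation of at least six hours, which lengthens that gap for the observed children.

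The contact schedule switches when a site crosses over, so it is tied to treatment. The fixed time effects and random site effects in Statistical methods do not remove a measurement change that coincides with the intervention indicator. This outcome carries the safety claim, and the planned contrast is small: 3% against 5%, with a margin of 7 percentage points.

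**Working it through.** **1. The plan's own figure.** Inputs from Sample size calculation: 11 sites, 12 months, 10 patients per site per month, control rate 3%, anticipated increase 2 points, margin 7 points, ICC 0.1, one-sided alpha 0.025.
- 11 × 12 × 10 = 1320, and 1320 / 0.95 = 1389.5, rounded up to 1390.
- Stepped-wedge (Hussey–Hughes) variance with one site switching per month: Var = I·s·(s + T·t) / [(I·U − W)·s + (U² + I·T·U − T·W − I·V)·t]. Here I = 11, T = 12, U = 66, W = V = 506, t = 0.1 × 0.0291 and s = 0.9 × 0.0291 / 10, with 0.0291 = 0.03 × 0.97.
- The standard error is 1.51 points. (7 − 2) / 1.51 − 1.96 = 1.35, which gives power 0.911.

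The stated size is reproduced and is not in question. The standard error serves below as a yardstick.

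**2. The clocks side by side.** For a child sent home from the ED, ED discharge and discharge home are the same moment. The effective conflict for these children is presentation against ED discharge. The third clock separates only for admitted children, and whether they belong in the denominator is itself stated in two ways.

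**3. Window still open at the query.** Let L be the hours from presentation to ED discharge, taking presentation as ED arrival.
- The window closes at 72 + L and the query is sent at 72, so the uncovered share is L/72.
- Observation in the ED gives at least 6 hours from arrival. With L = 6, the window closes at 78 hours, 66/72 = 91.7% has elapsed, and 8.3% is open.
- With L = 8, 11.1% is open; with L = 12, 16.7%. These two values of L are illustrative.

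**4. Re-visits hidden, upper limit.** Assume a constant hazard over the window, that every counted child is observed for L hours, that every parent answers at once, and that nothing is caught by the eCRF. The loss is rate × L/72.
- At the planned 5%: 0.42 points (L = 6), 0.56 (L = 8), 0.83 (L = 12).
- 0.42 points is 0.42/2 = 21% of the anticipated increase and 0.42/7 = 6% of the margin.

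**5. The control side.** The same formula applies to a control parent called at exactly 72 hours. The article gives no control ED stay.
- If no control is truncated, the difference between phases is 0.42 points.
- If every control also had L = 6 and was called at 72 hours, the control loss is 3% × 6/72 = 0.25 points and the difference is 0.17.
- A control called after 72 + L loses nothing.

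**6. Ceiling on the test.** At the margin (3% against 10%), the loss for L = 6 is 10% × 6/72 = 0.83 points. If all of it fell in the intervention phase, the one-sided error would rise from 0.025 as follows:
- 1.96 − 0.83/2.18 = 1.58, giving 0.057 (variance at 6.5%);
- 1.96 − 0.83/1.74 = 1.48, giving 0.069 (variance at 4%).

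This needs every assumption in step 4 and no truncation in controls. It is a bound and not an expected value.

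**The case against.** The loss is limited by design. Same-hospital returns enter the eCRF whenever they happen, so only visits to other providers depend on the contact. Many parents will answer later than 72 hours, and those who do not answer are called at 5 to 7 days, when a window of 78 hours or so has closed. Not every intervention-phase child is observed; some go home directly. The earliest control calls can also fall too soon. The control call uses the same documentation as the intervention phase, so the content of the questions is already largely aligned. All of this stands. It makes the figures above upper limits for the stated gap, but it does not remove the conflict between trigger and question or the difference in timing between phases.

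A reader might infer three stronger things.
- **That a large part of control follow-up is uncovered.** Combining the 2-day median stay with the discharge-home rule would leave 48 of 72 hours (67%) open at a 72-hour contact, or about a third of control window time at 50% admission. The documents do not support this. The discharge-home clock belongs to the eCRF route for same-hospital returns, which needs no contact, whereas the query refers to ED discharge. Calls may also come as late as day 7.
- **That the bias favours non-inferiority.** Truncated answers would lower the intervention count, but repeated app prompts could raise reporting. The net direction is open.
- **That presentation is the better time zero.** Treatment cannot move it, but a child admitted for 2 days could re-visit in only about 72 − 48 = 24 of the 72 hours, against 66 for a child sent home after six hours. It is a trade-off, not a correction.

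**Conclusion.** The point holds as an internal contradiction in the definition and collection of the second co-primary outcome. Time zero is worded in three ways and the denominator in two. The app query always goes out before its own window closes, by at least six hours for observed children. Prompt responders are not described as being asked again, so late re-visits elsewhere can be missed, on a contact schedule that changes with phase.

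The size is modest: at most about 0.4 points of a 5% rate for a six-hour gap, more if ED stays are longer. This rests on a constant hazard, immediate answers and no eCRF capture. It is small against the 7-point margin but not against an anticipated 2-point increase. It does not show that the non-inferiority test is invalid, nor which way the result would lean. It is worth correcting because a stated rule truncates the safety outcome and the correction is cheap.

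**What to change.** 1. Keep the ED-discharge clock given under Primary outcomes, and use it in the abstract, the eCRF re-activation rule, the rule for caregiver calls and the query text.
2. State whether admitted children count in the denominator. If they do, state from which discharge their 72 hours run, since leaving the ED for a ward and going home can be about 2 days apart.
3. Send the app query, and make the earliest control call, no sooner than 72 hours after the recorded ED discharge. Define one contact interval from that time point for both phases.
4. Record date and time for every reported visit, including those to other providers, so that visits outside the window can be removed in the analysis.
5. Use the linked billing data as a partial check of reported re-visits by phase.

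The cost is revised wording, a changed trigger in the app and the call schedule, one more dated item in the query and one validation table. The billing check reaches only patients of the participating insurers. The route of contact (app first, or telephone only) would still differ by phase and should be acknowledged when the result is interpreted.

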#### Statistical methods

##### Clinical evaluation

For the hospitalized patient group, the relative risk change due to the nCP for the binary endpoint “hospitalization” will be estimated using a GLMM with log link and modeling fixed effects for intervention and time as well as random study site effects. A Wald Z-test will be used to test the null hypothesis of equal hospitalization risk with and without the intervention at a significance level of *α* = 0.05. For the non-inferiority analysis with respect to the proportion of patients with unplanned re-visits, the absolute risk difference will be considered. A GLMM with an identity link for the binary endpoint of unplanned re-visits, again with fixed effects for intervention and time and random study site effects, will be applied. A one-sided 97.5% confidence interval will be estimated for the difference in unplanned re-hospitalization rates. If the non-inferiority margin is not overlapped by the confidence interval, the null hypothesis of inferiority will be rejected. The two endpoints will be tested co-primary, i.e., both statistical tests have to be significant for a study success. As co-primary testing does not inflate the type I error rate, there is no need to correct for multiple testing, while an overall power of more than 80% can be preserved assuming that the two tests are independent each with a power of 90% (power of 1 st COP times power of 2nd COP).

Secondary outcomes will be analyzed using appropriate statistical methods as specified in the statistical analysis plan (SAP) prior to the beginning of the study. Clinical documentation will be performed in the software tools designed for the SaVeBRAIN.Kids study to ensure high data quality.

Primary analyses will be conducted as intention to treat, comparing outcomes in patients recruited before and after the study sites’ staff introduction to the nCP according to the randomization. Study sites with major protocol violations (e.g., late or no training for the nCP) will be excluded from a sensitivity analysis of a per-protocol study population. Further details will be specified in the SAP.

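### Staff who know the phase recruit about 35% of eligible children without a stated approach rule, the described log of non-approached children starts only after the monthly target, and the primary models adjust for no patient factor

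*Protocol article*

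**What the plan says.** **Knowledge of phase.** All sites begin in the control phase and cross over in random order, with eight weeks' notice (Interventions). The core team and "attending local ED staff cannot be blinded for the assignment group" (Assignment of interventions and blinding). ED staff also hand out the study information, at triage (Recruitment).

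**Share recruited.** The sites see cases "with an average of 757 annual and 63 monthly cases". The target is 11 children per site-month, described as "representing approximately 35% of the eligible case volume after subtracting 50% of the total case number due to assumed ineligibility". On the ceiling, "a maximum number of 13 recruited patients per center per month will be allowed" (all Recruitment).

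**Children not recruited.** "After meeting the monthly recruitment target, the local study physicians will document eligible but non-approached cases" (Data collection and management). These entries are anonymous and use the study software. For the control phase, the Control group section says that screening is documented in the eCRF. It does not describe a list of eligible children who were not enrolled.

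**Analysis.** The hospitalization model is specified as "modeling fixed effects for intervention and time as well as random study site effects" (Clinical evaluation), and the re-visit model has the same terms. The primary analysis compares children recruited before and after the site's introduction to the nCP. The historical cohort is meant to show changes due to study awareness, training and use of the eCRF. The article says that it can help detect bias but does not prevent it.

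**The concern.** Randomising the order in which sites switch protects the comparison only if the children enrolled before and after the switch come from the eligible pool in the same way. Here the phase is known when a family is approached, and about two thirds of eligible children are not needed to meet the target.

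The setting gives reasons why enrolment could differ by phase. In the nCP phase, a child with a high symptom burden or neurological findings needs at least six hours of monitoring in the ED, so enrolling that child takes more staff time. Parents who feel unsure about going home may be less inclined to join a study built around home monitoring.

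A shift towards milder cases or more confident parents would lower the apparent admission risk, and could lower the re-visit proportion, with no effect of the pathway. Intention-to-treat analysis does not remove this, because it starts from the children who were recruited. The primary models have no term that would absorb it. Both co-primary results are exposed.

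**Working it through.** **1. The plan's own figure.** Eligible children per site-month: 63 × 0.5 = 31.5. Share enrolled: 11 / 31.5 = 34.9%, which reproduces the stated 35%. At the ceiling: 13 / 31.5 = 41.3%.

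**2. Effect of selective enrolment on the relative risk.** From the Sample size calculation section: control admission 50%, target relative risk 0.80. Assumptions of this review: no true pathway effect, control-phase enrolment unrelated to disposition, and overall enrolment of 35% in both phases. Let *h* be the nCP-phase enrolment probability of a child who would be sent home, and *a* that of a child who would be admitted. Then

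apparent admission = 0.5*a* / (0.5*a* + 0.5*h*), and apparent RR = apparent admission / 0.5.

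| *h* | *a* | Apparent admission | Apparent RR |
|---|---|---|---|
| 35% | 35% | 0.35/0.70 = 50.0% | 1.00 |
| 37.5% | 32.5% | 0.325/0.70 = 46.4% | 0.93 |
| 40% | 30% | 0.30/0.70 = 42.9% | 0.86 |
| 42% | 28% | 0.28/0.70 = 40.0% | 0.80 |

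In the last row, 11 × 0.40 = 4.4 would-be-admitted children are enrolled per site-month instead of 11 × 0.50 = 5.5, a difference of about one child.

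**3. Without perfect sorting.** Step 2 lets staff sort by eventual disposition. Suppose instead that they can tell only a higher-risk from a lower-risk group, each half of the eligible pool. The group admission rates are assumptions with a mean of 50%. If the higher-risk share among enrolled children falls by *d* in the nCP phase, apparent admission is 0.5 − *d* × (rate difference between groups).

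| Group admission rates | RR at *d* = 10 points | *d* needed for RR 0.80 |
|---|---|---|
| 90% / 10% | (0.5 − 0.08)/0.5 = 0.84 | 0.10/0.80 = 12.5 points |
| 80% / 20% | (0.5 − 0.06)/0.5 = 0.88 | 0.10/0.60 = 16.7 points |
| 70% / 30% | (0.5 − 0.04)/0.5 = 0.92 | 0.10/0.40 = 25 points |

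**4. What the planned data can show.** Baseline items of enrolled children can be compared by phase, and children logged after the target can be set beside enrolled children. Neither shows who was passed over while recruitment was open. On the article's wording, a site-month that never reaches its target produces no log.

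**5. Re-visits.** The documents give no basis for a numerical illustration. The direction depends on how severity and parental confidence relate to re-visits.

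**The case against.** The strongest reply is that the log sentence can be read more kindly. Eligible families may be approached as they arrive until the target is met, and only later arrivals are logged. Information at triage, before the examination and the disposition decision, fits that reading. Much of the remaining 65% would then be logged, and refusals and missed presentations would account for part of the rest. So the 35% does not mean that staff hand-pick one child in three. The full protocol may also hold a fuller screening log, and the SAP may add adjusted analyses.

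This stands in part. If approach is consecutive, the room for selection shrinks greatly, but the article does not say that it is. It does state the primary model terms, and no patient covariate is among them.

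The splits in the working are also assumptions. The mildest gives 0.93, well short of the target, and constant under-enrolment in both phases would not bias the contrast. That is accepted.

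A reader might infer that the planned data could not reveal such a bias. The documents do not support this: history, GCS and neurological findings are recorded for enrolled children, so a shift in recorded severity would be visible by phase. A shift in unrecorded traits such as parental confidence would not be, and covariate adjustment would not remove it either.

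**Conclusion.** The point holds as a weakness in the design as described. Recruiters know the phase, no approach rule is stated, the described logging begins only after the monthly target, and the primary models adjust for no patient characteristic. If enrolment depends on expected disposition differently in the two phases, both co-primary contrasts are biased, and neither the intention-to-treat principle nor the historical cohort corrects this.

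Under the assumptions of no true effect, 50% admission and neutral control enrolment, a 40%/30% split gives a relative risk of 0.86 and a 42%/28% split gives the target of 0.80. With imperfect sorting, the shift in case mix needed for 0.80 is 12.5 to 25 points over the group admission rates tried.

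The documents do not show that selection will occur or how large it would be. A conclusion that the trial's result will be an artefact of enrolment is not supported.

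**What to change.** 1. **Approach and log.** In both phases, approach eligible children consecutively until the monthly number is reached. Start the existing anonymous log with the first eligible child of each month, recording age, GCS, key symptoms and admission status.
2. **Adjustment.** Pre-specify adjustment of the hospitalization model for baseline eCRF items (age, GCS 14 versus 15, loss of consciousness, initial symptom burden) and report a standardised relative risk. For re-visits, report a covariate-standardised risk difference. Name a fallback in advance, because an identity-link model with an assumed event rate of about 3% may not converge.
3. **Check.** Compare enrolled with logged children by phase. Report hospitalization in all eligible children only as a supportive analysis. Non-enrolled children in the nCP phase did not receive the app, so that estimate is diluted.

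The cost is a short log entry for each eligible child not enrolled before the target is met, plus some extra modelling work. No additional patients or procedures are needed. Children already passed over cannot be logged prospectively, so the log should change promptly. If the full protocol already contains an approach rule and a complete log, saying so would settle item 1.
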